### Sample size and power calculations

The assumptions for the power calculations were that patients aged 65 and over represent 17% of the total population; that 40% of study population will be in the high risk group.

Also assuming that:

1. Minimum worthwhile change in detection rate was 1% for targeted screening versus routine practice. It is estimated that this change would equate to £10,000 per life year gained. This is based on the following assumptions:

a) 60% of new cases of identified AF would be suitable candidates for warfarin

b) Annual risk of stroke in this population was 5%, reduced by 60% to 2% if treated

c) Costs: £25 to screen a patient; £100 to treat with warfarin pa; £6,000 NHS costs to treat a stroke

2. 50% of patients with AF will be already known to their general practitioner (estimates range from 30% [19] to 76% [20])

3. Community prevalence of AF in this population was 6% [2]

See figure 1. It was assumed that the baseline prevalence of AF known to the practice (A1) would be 3% (i.e. half of real prevalence of 6%) and that the prevalence of known AF in the control practices would remain constant over the screening period. Thus, the change in the prevalence of known AF in the control practices between baseline to follow up (C2-C1) should be approximately 0%. The change in the GP educated arm (B2-A1) should be marginally higher and is assumed to be between 0 and 1%. The change in the systematic screening arm should, on average, be between 0 and 3% and was assumed to be approximately 2% for the total screening arm (A3-A1) and in the high risk arm (A2-A1) was approximately 3%.

All sample size calculations were for 90% power and 5% significance levels unless otherwise stated.

*a) To detect a 1% difference in detection rate between intervention (GP educated) and control practices (B2-A1) vs (C2-C1). *This requires 1,236 patients. However, since this is a difference based at the practice level of randomisation, it needed to be inflated by the design factor. Based on AF prevalence data from the EcHoES (Echocardiographic Heart of England Screening) Study [2], the between practice variance is 3.7 and the within practice variance is 246. This gave an intra-cluster correlation coefficient of 0.015. The most efficient design in this circumstance would be a cluster size of 200, which gives a design factor of 4. Therefore, 5,000 patients would be needed in 25 practices in both intervention (GP educated) and control groups.

*b) To detect a 1% difference in detection rate between intervention (Systematic screening **total** arm) and control practices (A3-A1) vs (C2-C1)*. This requires 1,236 patients but when scaled by the design factor of 4 required 5,000 patients.

*c) To detect a 1.8% difference in detection rate between intervention (Systematic screening **high risk ** arm) and control practices (A2-A1) vs (C2-C1)*. This requires 684 patients. However, since this is a difference based at the practice level of randomisation, it also needed to be inflated by the design factor. This meant that 2,736 patients would be needed in each arm. Since the ratio of patients in the two arms is 2:5 this means that 1,916 patients would be needed in the high risk arm and 4,789 in the control arm. With the 2,000 patients expected to be at high risk in this arm – resulting from the 5,000 needed for the previous comparison there were more than enough patients to detect the required difference.

Although comparison b) required fewer patients to detect the expected difference (2%) stated in the assumptions, it would be possible to detect differences as low as 1%, should the detection rate not be as high as expected.

The a), b) and c) comparisons are all at practice level randomisation.

*d) To detect a 1% difference in detection rate between high risk screening strategy and routine practice prompted by education (opportunistic arm) (A2-A1) vs (B2-A1).*This requires 1,236 patients in both the high risk systematic screening and the GP educated (opportunistic) screening arms of the intervention practices assuming the high risk screening detects a 1% increase and opportunistic screening detects 0% increase. Should the increased detection rates be higher in each arm (1.7% in the high risk arm and 0.7% in the opportunistic arm) then this could require 2,686 patients in each arm. However, since there is a ratio of 2:5 patients in these arms there will be sufficient patients as only 1,880 are needed in the high risk arm and 4,700 in the opportunistic arm to be able to detect this 1% difference*.*

e) To detect a 1% difference in detection rate between total screening strategy and routine practice prompted by education (opportunistic arm) (A3-A1) vs (B2-A1).This requires 3,300 patients in both the total screening and the GP educated (opportunistic) screening arms of the intervention practices.

*f) To detect a relative risk (RR) of 2 (1% detection rate difference) between total population and high risk screening (A3 vs A2).*It was assumed that 40% of the study population fall into the high risk group, and the prevalence of undetected AF is 3%. This meant that 1,434 patients would be needed in each of the two risk groups to detect a two fold difference in risk (i.e. RR of AF in high risk as compared to low risk group is 2). This RR of 2 equates to an increase in AF detection rate from 3% in the total population arm to 4% in the high risk arm. Since there was a 40:60 split in the two risk groups unequal sample size calculations only require a minimum of 1,200 patients in the high risk group and 1,800 in the moderate/low risk group. This was achievable with a screening arm of 5,000 patients, as there would actually be 1,320 in the high risk group and 1,980 in the moderate risk group if a 66% screening acceptance rate was assumed.

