## Background

Atrial fibrillation (AF) has been recognised as an important independent risk factor for thromboembolic disease, particularly stroke with which it is associated with a five fold increase in risk [1]. There are few data on the prevalence of AF in the United Kingdom. Local data derived from the Echocardiographic Heart of England Screening (ECHOES) study suggested a prevalence of AF in people over the age of 65 of 3.8% (95% CI: 2.5–5.1) [2]. A review of four large community based studies of AF suggested that the overall community prevalence in the United States is 0.89% [3]. In these studies, the prevalence increased sharply with age: 2.3% of people aged 40 or over; 5.9% of people aged over 65 (higher than the local estimate), and 10% of those over 80. The vast majority (84%) of people with AF are over the age of 65. AF is a particularly important risk factor for stroke in the elderly – while 15% of all strokes are associated with the arrhythmia, it is associated with 36% of strokes in people over the age of 80. The incidence of new cases of AF in people over the age of 65 is of the order of 1% per annum [4].

Screening for AF in the elderly fulfils many of the Wilson-Jungner criteria for a screening programme [5]. It is a common and important condition which can be diagnosed by means of a simple test, and the risk of serious sequelae such as stroke can be dramatically reduced by treatment.

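### The 6% AF prevalence is cited to a study the article itself reports at 3.8% (2.5–5.1); at 3.8%, comparison f) has about 75–78% power, not 90%

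*Protocol article*

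**What the plan says.** Assumption 3 under Sample size and power calculations reads "Community prevalence of AF in this population was 6% [2". The Background says that the local study "suggested a prevalence of AF in people over the age of 65 of 3.8% (95% CI: 2.5–5.1) [2". Both carry reference number 2. Comparison a) confirms which study that is: its cluster variances are "Based on AF prevalence data from the EcHoES (Echocardiographic Heart of England Screening) Study [2".

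The Background has one other prevalence for this age group, from a review of four US community studies (reference 3): "5.9% of people aged over 65 (higher than the local estimate".

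The 6% is then carried forward. Assumption 2 is that "50% of patients with AF will be already known to their general practitioner (estimates range from 30% [19] to 76% [20", so known AF at baseline "would be 3% (i.e. half of real prevalence of 6" (per cent). The same section bounds the gain from systematic screening at 0 to 3% and assumes about 2% for the whole arm and about 3% for the high-risk patients. Comparison f) assumes that "the prevalence of undetected AF is 3" (per cent), 40% of patients at high risk and a relative risk of 2. It concludes that the 1,320 high-risk and 1,980 moderate-risk patients expected at 66% uptake are enough.

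**The concern.** The article gives one source two different values for one quantity, and the value used for planning is above the source's own confidence interval. It is about 1.6 times the reported estimate (6/3.8 = 1.58). The trial runs in the West Midlands, and the article treats the local study as the local estimate.

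Comparison f) is where this matters. It addresses targeted against whole-population screening, a choice named in the primary objective, and the economic framework section says that the study was powered for it. If undetected AF is nearer 1.9% than 3%, f) has fewer events than planned, and the statement that its size is achievable fails. A non-significant f) could then be read as showing that the two strategies yield much the same, when the comparison was simply short of power.

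**Working it through.** **Inputs from the article.** Prevalence 6% (assumption 3) or 3.8%, CI 2.5–5.1 (Background); known share 50%, range 30% to 76%; high-risk share 40%; relative risk 2; 1,320 v 1,980 attenders; 5% significance and 90% power. Sidedness is not stated; two-sided is assumed.

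**Step 1: rates in the two risk groups.** With undetected AF u, p_low = u / (0.4 × 2 + 0.6) = u / 1.4 and p_high = 2 × p_low.
- At 6%: u = 6% × 0.5 = 3.0%; p_low = 2.143%, p_high = 4.286%.
- At 3.8%: u = 3.8% × 0.5 = 1.9%; p_low = 1.357%, p_high = 2.714%.

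**Step 2: reproduce the article's figure.** The standard two-proportion formula at 3% gives 1,422 per group without continuity correction. With rates rounded to 4.3% v 2.1% and the correction it gives 1,433. The article states 1,434. At 40:60 it gives 1,168 / 1,752 uncorrected, against the stated 1,200 / 1,800. The article's method is therefore recovered, with u = 3% as its input.

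**Step 3: power with 1,320 v 1,980.** With n = 1,320, k = 1.5 and difference d, power = Φ{[d√(nk) − 1.96√((k+1)u(1−u))] / √(k·p_high(1−p_high) + p_low(1−p_low))}. The pooled rate equals u because the split is 40:60.
- At 3.0%: (0.9535 − 0.5287) / 0.2872 = 1.479, power 93.0%.
- At 1.9%: (0.6039 − 0.4231) / 0.2302 = 0.785, power 78.4%.

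The table shows other values. In each range the lower figure has the continuity correction and the upper does not.

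| Prevalence | Known share | Undetected AF | Power of f) |
|---|---|---|---|
| 6% | 50% | 3.0% | 92–93% |
| 5.9% | 50% | 2.95% | 91–93% |
| 5.1% | 50% | 2.55% | 87–89% |
| 3.8% | 50% | 1.9% | 75–78% |
| 2.5% | 50% | 1.25% | 55–61% |
| 3.8% | 30% | 2.66% | 88–90% |
| 3.8% | 76% | 0.91% | 42–49% |

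**Step 4: what 90% power would take at 3.8% and 50% known.** For a relative risk of 2, about 1,870 high-risk attenders (1,990 with correction), against 1,320. The arm of 5,000 holds 5,000 × 40% = 2,000 high-risk patients, so uptake would have to be about 93% to 99% (1,870/2,000 and 1,990/2,000) rather than 66%. Alternatively, with 1,320 v 1,980, the relative risk detectable at 90% power is about 2.3–2.4.

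**Step 5: the assumed gains.** At 3.8% and 50% known, finding every undetected case yields 1.9% overall and 2.7% in the high-risk group at relative risk 2. The assumed gains of about 2% and 3% exceed both. Applying the 66% uptake from f) gives 1.9% × 0.66 = 1.25% and 2.714% × 0.66 = 1.79%. At 6% the same step gives 1.98% and 2.83%, close to the assumed 2% and 3%. The article does not say that it derived them this way, so this is a reconstruction.

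**Step 6: comparisons a) to e).** With continuity correction, 1% v 0% gives 1,236 (a, b and d), 1.8% v 0% gives 684 (c), and 1.7% v 0.7% gives 2,686 (d). These are the article's figures, and none uses the 6%. Comparison e) states only a 1% difference and 3,300 patients; 2% v 1% reproduces that number, but the article does not print those rates.

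**The case against.** The strongest reply is that the number may be right and the reference wrong. The 5.9% of the US review rounds to 6%, and at 5.9% with half known f) has 91–93% power. This stands as a limit on the point. The article does not show which source was meant, so f) is overstated relative to the local estimate and not proved wrong outright. A miscitation would still leave unexplained why the higher, non-local figure was preferred in a local trial.

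The second reply concerns reach. A reader might infer that the whole sample size fails. It does not. The 5,000 per arm comes from a) and b), which are sized on a 1% difference. The article says itself that b) can detect differences as low as 1% if detection is lower than expected. The reconstructed gain of 1.25% still exceeds 1%, and 1.79% about equals the 1.8% in c).

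A reader might also infer that e) is undermined because a 2% yield would exceed the undetected AF. The article states no such yield in e), and for a fixed 1% difference lower rates need fewer patients (1.9% v 0.9% needs 3,096 with correction, against 3,300).

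Finally, a reader might conclude that every prevalence in the local interval misses 90%. That holds only with half of AF known. If 30% is known, power is about 96% at 5.1% and 88–90% at 3.8%.

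It is also fair to say that f) compares risk groups within the screened arm and is not a randomised contrast. It remains a comparison that the article says it was powered for.

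**Conclusion.** The contradiction is established from the article alone: reference 2 is given as 6% in one section and 3.8% (2.5–5.1) in another. The consequence is confined to the expected gains and to comparison f). On the local figure, f) has about 75–78% power for a relative risk of 2, some 15 to 17 points below what the 6% implies, and the assumed gains of 2% and 3% are larger than complete detection could deliver.

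These figures assume a two-sided 5% test, 50% known AF, a 40:60 split and 66% uptake. They are sensitive to the known share: over the article's own 30% to 76% range, power at 3.8% runs from 88–90% down to 42–49%. The documents do not support the reading that f) is wrong whatever the source, or that the trial as a whole is too small.

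**What to change.** - State which source the prevalence comes from and correct the reference.
- Use the local 3.8% (2.5–5.1) as the base case: known AF 1.9%, undetected AF 1.9%. Keep about 6% as a scenario, cited to its true source.
- Restate the expected gains so that they stay within the undetected AF: about 1.25% overall and 1.8% in the high-risk group, if the 66% uptake is applied.
- Restate f) as about 75–78% power for a relative risk of 2, or 90% power for a relative risk of about 2.3–2.4, and show the result at 30% and 76% known.
- Leave a) to e) as they are.

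The cost is a revision of the text in the sample size section. No more patients are needed, and the only downside is a less favourable stated power for f).

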### Statistical analysis

Intention to treat analysis will be used.

Any previously known Atrial Fibrillation cases will be subtracted from the totals obtained at the end of the study to ensure there is no double counting in the incidence figures.

Chi-squared, independent t-tests and log-linear models will be used to describe demographic data. If there are differences between the groups this may need to be adjusted for in later analyses.

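### Comparisons a) and b) reach 90% power for a 1-point difference only by setting the new-case rate in control practices, and so its variance, to exactly zero

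*Protocol article*

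**What the plan says.** All of the following is in the Protocol article.

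- *Sample size and power calculations* takes as its premise that "the prevalence of known AF in the control practices would remain constant over the screening period", and concludes that "the change in the prevalence of known AF in the control practices between baseline to follow up (C2-C1) should be approximately 0" per cent.
- The same section states: "All sample size calculations were for 90% power and 5% significance levels unless otherwise stated".
- Comparison a) (GP-educated v control) and comparison b) (total systematic screening v control) each need 1,236 patients for a 1-point difference. The design factor of 4 raises this to about 5,000 per arm in 25 practices. For b) the section adds that "it would be possible to detect differences as low as 1%, should the detection rate not be as high as expected".
- Comparison d) attaches the same 1,236 to a 1% increase against a 0% increase, and gives 2,686 if the rates are 1.7% and 0.7%.
- Comparison e), for another 1-point difference, states: "This requires 3,300 patients in both the total screening and the GP educated (opportunistic) screening arms".
- *Outcome measures* names the incidence of AF as a primary outcome. *Statistical analysis* says: "Any previously known Atrial Fibrillation cases will be subtracted from the totals obtained at the end of the study". *Computerised and note searches of GP records* runs the same searches in intervention and control practices before screening starts and 12 months after.
- *Background* says: "The incidence of new cases of AF in people over the age of 65 is of the order of 1% per annum [4".

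**The concern.** The zero rests on a statement about net prevalence: the stock of known AF in control practices stays level. The analysis counts something else, namely patients not known to have AF at baseline who are known to have it a year later. A death or removal of a known case lowers the stock, but it does not cancel a new diagnosis once known cases have been subtracted. Steady prevalence is therefore compatible with any number of new diagnoses.

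This matters because the variance of a rare proportion is nearly proportional to the proportion itself. Setting the control rate to 0% removes the control arm's variance altogether, so a small departure from zero raises the required number quickly. Comparisons a) and b) are the contrasts with routine practice and also carry the fourfold clustering penalty, so they have little margin. A non-significant result in a) would come from a test weaker than its stated 90%.

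**Working it through.** **Inputs.** Two-sided 5% significance and 90% power (the document does not state sidedness; two-sided reproduces its figures). Difference d = 0.01. ICC 0.015 and 200 patients per practice give 1 + 199 × 0.015 = 3.985, stated as 4. With 5,000 per arm, the effective number is 5,000 / 4 = 1,250 per arm.

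**Formula.** With p̄ = (p1 + p2)/2:

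n0 = [1.960 √(2p̄(1−p̄)) + 1.2816 √(p1(1−p1) + p2(1−p2))]² / d²

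continuity-corrected n = (n0/4) [1 + √(1 + 4/(n0 d))]²

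**Reproducing the plan's figure (0% v 1%).** 2p̄(1−p̄) = 0.00995 and p1(1−p1) + p2(1−p2) = 0 + 0.0099. Then n0 = (0.1955 + 0.1275)² / 0.0001 = 1,043.4. The corrected n is 1,235.3, rounded up to **1,236**, and × 4 = 4,944, or about 5,000. The same formula returns the plan's 684 (0% v 1.8%), 2,686 (0.7% v 1.7%) and 3,300 (1% v 2%), so the method is identified.

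**Changing only the control rate.** For 1% v 2% the variance sum is 0.0099 + 0.0196 = 0.0295, about three times the 0.0099 above. n0 is 3,102.9 and the corrected n is 3,300.

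The control rates below are assumptions. Power is at effective n = 1,250, with and without the continuity correction. The detectable difference inverts the corrected formula at 90% power.

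| Control v intervention | Corrected n per arm | × 4 | Power for 1 point at 5,000 per arm | Detectable at 90% |
|---|---|---|---|---|
| 0% v 1% | 1,236 | 4,944 | 90–94% | 1.0 point |
| 0.1% v 1.1% | 1,445 | 5,780 | 85–90% | 1.1 points |
| 0.25% v 1.25% | 1,757 | 7,028 | 76–83% | 1.3 points |
| 0.5% v 1.5% | 2,274 | 9,096 | 64–71% | 1.5 points |
| 1% v 2% | 3,300 | 13,200 | 47–54% | 1.9 points |

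A control rate of only 0.1% already takes the requirement above 5,000.

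**Reserve in comparison b).** The plan expects a change of about 2% in the total screening arm (A3-A1). That is a change within the arm, not an excess over control. If the screened arm exceeds control by 2 points, power is 93–95% at 1% v 3%. If the 2% is the whole change in the screened arm, the excess shrinks as the control rate rises. At 0.5% in control it is 0.5% v 2% (1.5 points, 89–92% power). At 1% in control it is 1% v 2% (1 point, 47–54% power).

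**Dependence on the design factor.** The ICC was estimated from AF prevalence data, and the document gives none for new cases. As an illustration, at design factor 3 (ICC about 0.01) power for 1 point is 78–83% at control 0.5% and 61–66% at control 1%. At design factor 2 (ICC about 0.005) it is about 93–95% and 80–83%. A higher ICC would lower power further.

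**The case against.** **The 0% is an open assumption about a different quantity.** It concerns the net change in known AF, whereas the 1% a year in *Background* is the incidence of AF, not of AF diagnosed in routine care. A reader might infer that the document flatly contradicts itself and that 1% should replace 0%. It does not support that. The control rate could lie anywhere between the two. A value of 0.5% borrows the assumed 50% of AF already known, for which the document itself cites 30% to 76%, and a share of prevalent cases is not the share of incident cases recognised within a year. What remains is the mismatch: a premise about net prevalence sizes a comparison of new cases. Even on a net reading, a zero built from gains offset by losses has positive variance, while the formula gives it none.

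**The design factor may not carry over.** This stands. The power figures hold at the plan's own factor of 4 and would change with an ICC for new cases, in either direction.

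**The planners knew that the base rate matters.** Comparison d) raises it and e) uses 3,300. That is true, but neither check was carried to a) or b).

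**A null result in a) need not be read as no worthwhile effect.** The document defines its minimum worthwhile 1% for targeted screening against routine practice, not for a), and nowhere says how a non-significant a) would be read. So 1 point serves here only as the target a) was sized for.

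**No estimate is biased.** Correct. The planned analysis compares observed detection rates and does not use the 0%. Only the stated power is affected.

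**Conclusion.** The point holds as a mis-stated power claim. The 1,236 requires a control rate of exactly zero, which the counting rule and the 12-month interval make untenable. At design factor 4, the stated 90% for a 1-point difference becomes 85–90% at a control rate of 0.1% and falls to 47–54% at 1%. The statement that b) can detect differences as low as 1% therefore does not hold unconditionally. Comparison a), whose expected gain is between 0 and 1%, has no reserve. Comparison b) keeps about 93% or more only if the screened arm exceeds control by 2 points. Comparison c)'s 684 uses the same zero.

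The direction is certain; the size rests on two things the document does not supply, a routine new-diagnosis rate and an ICC for new cases. It would go too far to call the trial's true power 47–54%, or to treat 0.5–1% as the correct control rate.

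**What to change.** 1. Replace the 0% control rate with a stated non-zero range, labelled as an assumption, for new diagnoses over 12 months in routine care.
2. Restate the power or detectable difference of a) and b) as conditional on that rate and on the design factor, and note that the ICC comes from prevalence data. At factor 4, the difference detectable at 90% is about 1.5 points at a control rate of 0.5% and 1.9 points at 1%.
3. Remove the unconditional claim that b) can detect differences as low as 1%. Say that its power of about 93% or more needs a 2-point excess over control, and that a 2% change in the screened arm against 1% in control is a 1-point difference.
4. Interpret a) by its confidence interval against the 1-point target it was sized for, not by significance alone.

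Cost: wording only. The sample, data collection and analysis do not change; the stated power becomes less favourable.

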#### Randomisation

Randomisation of practices and patients was performed by statisticians from the Department of Primary Care and General Practice at The University of Birmingham. Cluster randomisation of practices to intervention or control was stratified by Townsend quartiles and practice size. Computer searches were carried out to identify cases of known AF, within the sample of patients identified above, using a published strategy [15]. The randomisation of patients within the intervention practices ensured that the study patients in each practice were divided equally between systematic and opportunistic screening arms and also that there was an even distribution of patients with known AF between the two arms. Patients within the systematic screening arm were identified by computerised record searching as either being at high risk (target population) or moderate risk (non-target population) of AF by recognised criteria [28,11].

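### Comparison d), and c) with the same structure, sets high-risk systematic patients against a whole all-risk arm, so part of d)'s planned difference is case mix rather than an effect of strategy

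*Protocol article*

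**What the plan says.** The sample-size section assumes "that 40% of study population will be in the high risk group" and sets 1% as the smallest worthwhile gain for targeted screening over routine practice.

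- **Comparison c)** contrasts A2-A1 (high-risk patients of the systematic arm) with C2-C1 (control practices). It starts from a difference of 1.8% ("This requires 684 patients"), applies a design factor of 4, and continues: "Since the ratio of patients in the two arms is 2:5 this means that 1,916 patients would be needed in the high risk arm". The control arm needs 4,789. The text classes c) with a) and b) as comparisons at practice-level randomisation.
- **Comparison d)** contrasts A2-A1 with B2-A1 (opportunistic arm). At 1.7% v 0.7% it needs 2,686 per arm at equal allocation, and the 2:5 ratio is then used to say that "only 1,880 are needed in the high risk arm and 4,700 in the opportunistic arm", so that numbers are sufficient.

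The section takes the relative risk of AF, high v low risk, as 2 (comparison f). It puts the change in the opportunistic arm between 0 and 1%. For the control practices it states that "the change in the prevalence of known AF in the control practices between baseline to follow up (C2-C1) should be approximately 0"%.

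Under Randomisation, risk classification is described for one arm only: "Patients within the systematic screening arm were identified by computerised record searching as either being at high risk (target population"). Allocation within practices was balanced on known AF, not on risk group. Statistical analysis names t-tests and random-effects ANOVA with no restriction by risk, and says only that demographic differences may need adjustment.

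**The concern.** The 2 in the 2:5 ratio is the 2,000 high-risk patients expected among 5,000 in the systematic arm. The 5 is a full control or opportunistic arm, in which 60% are not at high risk. Randomisation makes whole arms comparable. It does not make the high-risk part of one arm comparable with all of another.

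High-risk patients have more AF to find whatever method is used. A difference in d) therefore mixes two things: whether systematic invitation finds more than prompted pulse-taking, and whether high-risk patients have more undetected AF. The second is already known from the way the group is defined. The contrast bears on the primary objective (targeted screening v routine practice), and its detection difference would feed the incremental cost per case detected.

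**Working it through.** **1. Reproduce the plan's sizes.** Inputs: "All sample size calculations were for 90% power and 5% significance levels unless otherwise stated"; two-sided test of two proportions with continuity correction.

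- 1.8% v 0%: 684 per arm. With design factor 4: 684 × 4 = 2,736.
- 1.7% v 0.7%: 2,686 per arm.
- Unequal arms with k = 5/2: smaller arm = n(1 + k)/(2k) = 0.7n, larger arm = 2.5 times that.
- c): 2,736 × 0.7 = 1,915 and 4,788 (plan: 1,916 and 4,789).
- d): 2,686 × 0.7 = 1,880 and 4,700 (plan: the same).

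The arithmetic is right for its inputs. It also confirms that the comparator is the whole arm.

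**2. Enrichment under the plan's assumptions.** With low-risk rate r and high-risk rate 2r, the all-patient rate is 0.4 × 2r + 0.6 × r = 1.4r. High-risk over all = 2/1.4 = 1.43. The plan's expected changes agree with this: 2% in the total systematic arm × 1.43 = 2.86%, against its stated 3% for high risk.

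**3. Comparison d) with no difference between strategies.** SE = √[p₁(1 − p₁)/2,000 + p₂(1 − p₂)/5,000]; rejection ≈ Φ(difference/SE − 1.96).

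- Opportunistic 0.7%: the same process gives 0.7 × 1.43 = 1.0% in high-risk patients. Difference 0.30 points, SE 0.252, z = 1.19, rejection 22% (27% with a pooled null SE).
- Opportunistic 1% (top of the plan's range): 1.43% v 1.0%. Difference 0.43, SE 0.300, z = 1.43, rejection 30% (35% pooled).
- Opportunistic 0%: no case-mix difference.

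At 0.7%, the case-mix share of the 1.0-point target is 0.18 points for a relative risk of 1.5, 0.30 for 2 and 0.47 for 3.

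**4. Comparison c).** If the control change is 0%, 1.43 × 0 = 0, so case mix adds nothing on the new-case scale. If control practices record the roughly 1% annual incidence given in Background, high-risk patients would show 1.43% v 1.0% without screening. Design factors at the plan's intra-cluster correlation of 0.015:

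- 80 high-risk patients per practice: 1 + 79 × 0.015 = 2.185, effective n = 2,000/2.185 = 915.
- 200 controls per practice: 1 + 199 × 0.015 = 3.985, effective n = 5,000/3.985 = 1,255.

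SE 0.482, z = 0.89, rejection about 14% (16% pooled; about 11% with continuity correction).

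**5. Power for high-risk v high-risk, 2,000 v 2,000.** Ranges run from with to without continuity correction.

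- d), 1.7% v 0.7% both among high-risk patients: about 79–83%.
- d), 1.7% v 1.0%, if 0.7% is the all-risk rate: about 43–48%; about 5,990 per arm needed for 90%.
- c), 1.8% v 0%, design factor 4 (effective 500 per arm): about 85% without continuity correction, 76% with it; 2,736 per arm needed.
- c), design factor 2.185 (effective 915 per arm): about 97–98%; 684 × 2.185 = 1,495 per arm needed.

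**The case against.** Targeting works by choosing patients with more disease, so a higher yield per person screened is a legitimate result. Comparison f) measures that enrichment openly, and the economic question is cost per case detected. The economic section describes the trial as powered for targeted v population and systematic v routine screening; it does not name d). All of this stands, and it narrows the fault to reading the d) difference as the effect of a strategy.

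A reader might infer more than the documents support:

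- **That c) is biased as d) is.** The comparator is equally mismatched, but under the plan's 0% control change the case-mix bias is nil. The individual-level rejection rates for d) do not carry over to a clustered comparison.
- **That most of the 1-point target in d) is spurious.** At a 2% yield in both arms the shift would be 2.86 − 2.0 = 0.86 points, with rejection of about 53%. But 2% is the rate assumed for the total systematic arm; the opportunistic arm is put at 0 to 1%.
- **That high-risk patients show a change before any screening.** One baseline is subtracted throughout ("baseline prevalence of AF known to the practice (A1) would be 3"%). If A1 is an all-risk figure and known AF is also twice as common in high-risk patients, A2-A1 would begin at 4.29 − 3 = 1.29 points. But Figure 1, which defines A1, is not available, the relative risk for known AF is an assumption, and Statistical analysis says previously known cases are removed.
- **That the trial's main comparisons fail.** Comparisons a), b) and e) contrast whole randomised arms.

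**Conclusion.** The point holds, most clearly for d). As written, d) is not a randomised like-for-like contrast. With a relative risk of 2, 40% at high risk and a 0.7% opportunistic rate, 0.3 of its planned 1.0 points is case mix, and the chance of a significant result with no strategy effect is about 22–27% rather than 5%. That becomes about 30–35% at a 1% rate and falls to the nominal level at 0%.

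For c) the comparator is mismatched and the practice-level randomisation label does not cover it. Bias in the estimate depends on control practices finding new cases; at 1% the rejection rate is about 14–16% after allowing for clustering, or about 11% with continuity correction.

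These figures assume that detection in each risk group is proportional to its underlying AF, and that the published text is complete in describing risk classification for the systematic arm only.

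**What to change.** 1. Apply the same baseline, record-based risk classification to the opportunistic and control lists, and define c) and d) as high-risk v high-risk.
2. To judge targeted screening as a programme, count the cases found over the whole arm. At the plan's figures, 40% × 3% = 1.2% of the population, to set beside the 2% expected from total screening.
3. Restate power from step 5 of the working, saying for d) whether 0.7% refers to all patients or to high-risk patients. Withdraw or qualify the statement that numbers are sufficient. For c), state which design factor applies to about 80 patients per practice.
4. Stop describing c) as a comparison at practice-level randomisation unless it is redefined as above.

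The cost is lower stated power for d) and a wider record search. The current searches of all 15,000 records look for AF and selected prescriptions. Risk status also needs diagnoses such as heart failure, hypertension and diabetes, in about 10,000 further patients, and Background says only some practices keep disease registers. That is more than one extra query, but it uses records already being searched and needs no new patients.
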